### Follow-up

#### Data collection points

All data collection points are displayed in Fig. 1, based on the Standard Protocol Items: Recommendations for Interventional Trials (SPIRIT) guideline [108].Screening period: +/- 3 days before the interventionIntervention period: 12 weeksFollow-up period: none

**Fig. 1 Fig1:**
[figure not shown]
Data collection points for a polyherbal supplementation intervention for prediabetic adults

### Outcome measures

Outcome measures include glycemic parameters, lipids, inflammation, and progression to T2D (Table 2). A number of glycemic parameters in addition to fasting blood glucose and HbA_1c_ are measured throughout this study. Because insulin resistance often sets the stage for progression to T2D by placing a high demand on insulin-producing (β) beta-cells during a prediabetic state, we are using the validated HOMA-IR to estimate insulin resistance (calculated as: (Fasting insulin [μU/L] × Fasting blood glucose [nmol/L])/22.5 [109]). Likewise, the validated Quantitative Insulin Sensitivity Check Index **(**QUICKI) measurement to assess insulin sensitivity has also been used extensively, including in herbal dietary supplement clinical trials, and is (calculated as: 1/Log-fasting blood glucose [mg/dL] + Log-fasting insulin [μU/mL]) [109]. Additionally, pancreatic β-cells produce insulin. Thus, participant HOMA-β is being estimated as well (calculated as: (20 × Fasting insulin [μU/L])/(Fasting blood glucose [mmol/L] – 3.5) [109]).

**Table 2 Tab2:** Primary and secondary outcomes

Endpoint events	
Primary outcomes	
Glycemic parameters	Normal range reference
Fasting blood glucose	< 100.9 mg/dL
Glycosylated hemoglobin/HbA_1c_	< 5.7%
Fructosamine	200–285 μmol/L [63]
GlycoMark	~ 180 mg/dL
Fasting insulin	< 25 μU/L
Absence of high HOMA-Insulin Resistance	General US adult population: < 2.73 vs. ≥ 2.73 [63]
Quantitative Insulin Sensitivity Check Index	~ 100% [66]
Pancreatic β-cell function	~ 100% [66]
Secondary outcomes	
Lipid profile	
Total cholesterol	≤ 19 years: < 170 mg/dL; ≥ 20 years: 125–200 mg/dL
Low-density lipoprotein	< 100 mg/dL
High-density lipoprotein	≤ 19 years: > 45 mg/dL; ≥ 20 years men: ≥ 40 mg/dL; ≥ 20 years women: ≥ 50 mg/dL [129]
Triglycerides	< 150 mg/dL [130]
Inflammation	
High-sensitivity C-reactive protein (hs-CRP)	Varies^a^
Progression to type-2 diabetes (T2D) (according to 2016 ADA diagnostic criteria [39, 40])	

*ADA* American Diabetes Association*, HbA*_*1c*_ glycated hemoglobin/HbA1c, *HOMA-IR* homeostatic model of Insulin Resistance, *US* United States

^a^Elevated CRP levels indicate increased risk of T2DM [131] with normal CRP range 0.0–5.0 mg/L [132], while hs-CRP reference values applicable to cardiovascular risk assessment are < 2.0 mg/L [133]

Other relevant glycemic parameters required to gain a well-rounded understanding regarding potential impacts of the intervention include fructosamine and GlycoMark. Fructosamine is the concentration of plasma glucose over the lifetime of the protein, and represents the degree of glycation in many serum proteins involved in glucose synthesis. It is a test utilized in clinical practice and clinical studies of natural products [31, 110], is often viewed as an adjunct to HbA_1c_ (a measurement which is recommended every 3 months in clinical practice and reflects longer-term glycemic change over several months [34]) and fasting glucose measurements (short-term glycemic change), and reflects intermediate-term (previous 2–3 weeks) glycemic change. GlycoMark, a blood test used in clinical practice to determine peak hyperglycemia, provides accurate recognition of recent glycemic deterioration or improvement (within the previous 1–2 weeks) [111–113].

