#### Additional indicators

Incidence of T2D, calculated using the following formula: $$ \mathrm{Incidence}\ \mathrm{of}\ \mathrm{diabetes}\ \mathrm{mellitus}=\mathrm{Cases}\ \mathrm{of}\ \mathrm{diabetes}\ \mathrm{mellitus}\ \mathrm{at}\ \mathrm{end}\ \mathrm{of}\ \mathrm{study}/\mathrm{Total}\ \mathrm{cases}\ \mathrm{of}\ \mathrm{each}\ \mathrm{group}\times 100\% $$Reversion rates of each continuous parameter after 12 weeks (including reversion from prediabetes to normal glucose tolerance), calculated using the following formula: $$ \mathrm{Reversion}\ \mathrm{rate}=\mathrm{Cases}\ \mathrm{of}\ \mathrm{parameter}\ \mathrm{that}\ \mathrm{have}\ \mathrm{returned}\ \mathrm{to}\ \mathrm{normal}\ \mathrm{range}/\mathrm{Cases}\ \mathrm{of}\ \mathrm{each}\ \mathrm{group}\times 100\% $$

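### QUICKI is printed without the bracket around its sum and given a normal value the bracketed index cannot reach; conflicting units for HOMA-IR, HOMA-β and insulin break their cut-offs

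*Protocol article*

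**What the plan says.** The Outcome measures section of the protocol article gives formulas for three derived indices, and Table 2 lists all three as primary outcomes with reference values.

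- **QUICKI** is printed as "1/Log-fasting blood glucose [mg/dL] + Log-fasting insulin", with insulin in μU/mL. The same sentence presents it as a "measurement to assess insulin sensitivity has also been used extensively", so higher values should mean greater sensitivity. Table 2 gives its normal value as about 100%.
- **HOMA-IR** is printed as "Fasting insulin [μU/L] × Fasting blood glucose [nmol/L])/22.5". Table 2 makes the outcome the absence of a high value, with the cut-off "General US adult population: < 2.73 vs. ≥ 2.73".
- **HOMA-β** is printed as 20 times insulin in μU/L, divided by glucose in mmol/L minus 3.5. Table 2 gives about 100% as normal.
- **Fasting insulin** has a normal limit in Table 2 of below 25, labelled μU/L.

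The reference values are put to use. The Additional indicators section plans "Reversion rates of each continuous parameter after 12 weeks", counting participants whose value has returned to the normal range. The Statistical analysis methods section compares continuous outcomes by t test, or by the Wilcoxon-Mann-Whitney test or after transformation, and by a mixed model.

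**The concern.** There are two separate problems.

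The first is QUICKI. Under ordinary operator order the printed expression is the reciprocal of log glucose, plus log insulin. That is a different variable from the reciprocal of the sum. It moves up with insulin, whereas an insulin sensitivity index should move down. If the derivation code follows the printed text, a supplement that lowers fasting insulin would tend to look as if it worsened insulin sensitivity. If the code uses the bracketed form instead, the reference of about 100% is out of reach and the reversion rate carries no information.

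The second is units. Within one section insulin is in μU/mL for QUICKI but μU/L for both HOMA indices and for the Table 2 limit, and glucose is in nmol/L for HOMA-IR but mmol/L for HOMA-β. The numerical references only make sense on one of these scales. Any analysis that compares a participant's value with a reference depends on which scale is used.

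**Working it through.** **Inputs.** The formulas, units and reference values are those printed in Outcome measures and Table 2. Glucose of 100–125 mg/dL is the entry range; 70 mg/dL is added as an assumed low value. Assumptions, not in the document: fasting insulin of 2–25 μU/mL, a conversion of 18.016 mg/dL per mmol/L, and base-10 logs (the document says only Log).

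**1. QUICKI direction, glucose fixed at 100 mg/dL (log10 = 2).**

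| Insulin, μU/mL | Printed: 1/log G + log I | Bracketed: 1/(log G + log I) |
|---|---|---|
| 5 | 0.5 + 0.699 = 1.20 | 1/2.699 = 0.371 |
| 10 | 0.5 + 1 = 1.50 | 1/3 = 0.333 |
| 15 | 0.5 + 1.176 = 1.68 | 1/3.176 = 0.315 |
| 25 | 0.5 + 1.398 = 1.90 | 1/3.398 = 0.294 |

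The printed form rises with insulin and the bracketed form falls. Natural logs give the same directions (printed 1.83 to 3.44, bracketed 0.161 to 0.128).

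For glucose the printed form keeps the right direction. At insulin 10 μU/mL it goes from 1.500 at 100 mg/dL to 1.477 at 125 mg/dL, a fall of 0.023. Moving insulin from 10 to 15 μU/mL at 100 mg/dL raises it by 1.676 − 1.500 = 0.176. Insulin therefore dominates the printed index.

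**2. QUICKI reference.** The bracketed index is highest at 70 mg/dL and 2 μU/mL: 1/log10(140) = 0.466. It is lowest at 125 mg/dL and 25 μU/mL: 1/log10(3125) = 0.286. A value of 1.0 needs glucose × insulin = 10, which is insulin of 0.1 μU/mL at 100 mg/dL (0.14 at 70, 0.08 at 125). No participant in the assumed range comes near it. The printed form does reach 1.0, at insulin of 10^(1 − 1/2) = 3.16 μU/mL for glucose 100 mg/dL.

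**3. HOMA-IR units.** Take 100 mg/dL = 5.55 mmol/L = 5.55×10^6 nmol/L, and 10 μU/mL = 10^4 μU/L.

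- With μU/mL and mmol/L: 10 × 5.55 / 22.5 = 2.47. The 2.73 cut-off is reached at 2.73 × 22.5 / 5.55 = 11.1 μU/mL.
- With the printed units: 10^4 × 5.55×10^6 / 22.5 = 2.47×10^9.
- The ratio is 10^3 × 10^6 = 10^9. If only the glucose unit is wrong, it is 10^6.

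In the printed units no participant could be below 2.73.

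**4. HOMA-β units.** With μU/mL: 20 × 10 / (5.55 − 3.5) = 97.5, on the scale of the reference. With μU/L: 97,531, which is 1,000-fold higher.

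**5. Insulin limit.** An insulin of 25 μU/L is 0.025 μU/mL. At 100 mg/dL, with glucose in mmol/L, that gives HOMA-IR = 0.025 × 5.55 / 22.5 = 0.006 and HOMA-β = 20 × 0.025 / 2.05 = 0.24, far from 2.73 and 100. Table 2's own references therefore fit together only if the limit is in μU/mL.

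**6. Effect on tests.** Wrong units multiply HOMA-IR and HOMA-β by a constant. The t statistic, the ranks and the mixed-model test are unchanged; after a log transformation the constant is only a shift. The missing QUICKI bracket is not a rescaling and does change the tests.

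**The case against.** The strongest reply is that these are printing slips. The indices are called validated and carry a citation, the same section already contains μU/mL and mmol/L, and a programmer would notice HOMA-IR values in the billions. That is fair for the units: they can be reconciled from the section itself, and the constant factors leave the continuous comparisons untouched. It is less reassuring for the bracket. The printed QUICKI gives values between 1 and 2, which look unremarkable and would not alert anyone.

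Three stronger readings are tempting, and the document does not support them.

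- A reader might infer that three primary comparisons are spoiled. Only QUICKI's continuous comparison is at risk. HOMA-IR and HOMA-β are affected only where values meet a cut-off.
- A reader might infer that QUICKI is both reversed and unable to reach 100%. These belong to different implementations: the printed form is reversed in insulin but reaches 1.0 near 3.2 μU/mL, while the bracketed form has the right direction but cannot reach 1.0. The 0% reversion applies only to the bracketed form.
- A reader might infer that the 100% entry was carried over from the β-cell row below it. The two entries match, but how that came about is not shown.

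Nothing in the document shows which form the analysts actually coded.

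**Conclusion.** The point stands in this limited form. As printed, QUICKI is not an insulin sensitivity index: it rises with insulin, though it still falls with glucose, and its group comparison could have the wrong sign. When bracketed it lies at about 0.29–0.47 for glucose 70–125 mg/dL and assumed insulin 2–25 μU/mL. The Table 2 normal of about 100% then gives a reversion rate of 0% in both arms, on any reading that requires a value near 1.0; the table states neither direction nor margin. The printed units put HOMA-IR 10^9-fold and HOMA-β 1,000-fold off their references and misstate the insulin limit. That breaks the HOMA-IR classification and the reversion rates if applied literally, but does not alter p-values for the continuous outcomes. The sample size is set in standard deviation units and is unaffected. The numerical ranges rest on the assumed insulin values and base-10 logs; the direction of the QUICKI error does not depend on the log base.

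**What to change.** - State QUICKI = 1/[log10(glucose, mg/dL) + log10(insulin, μU/mL)], naming the log base.
- State HOMA-IR = insulin (μU/mL) × glucose (mmol/L)/22.5, and HOMA-β = 20 × insulin (μU/mL)/(glucose (mmol/L) − 3.5).
- Change the Table 2 fasting insulin unit to μU/mL.
- Replace the QUICKI reference with a value on the index's own scale and for the stated log base, or drop QUICKI from the reversion analysis.
- Check the derivation code against these definitions before the planned unblinded interim look and before the final analysis.

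The cost is a short protocol correction and a code check. No new data are needed and the sample size does not change.

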#### Safety indices

Alanine aminotransferase (ALT) levels to assess hepatic functionAspartate aminotransferase (AST) levels to assess hepatic function

Both safety indices will be tested on visit 1 (baseline visit) and visit 2 (at 12 weeks).

#### Additional indicators

Incidence of T2D, calculated using the following formula: $$ \mathrm{Incidence}\ \mathrm{of}\ \mathrm{diabetes}\ \mathrm{mellitus}=\mathrm{Cases}\ \mathrm{of}\ \mathrm{diabetes}\ \mathrm{mellitus}\ \mathrm{at}\ \mathrm{end}\ \mathrm{of}\ \mathrm{study}/\mathrm{Total}\ \mathrm{cases}\ \mathrm{of}\ \mathrm{each}\ \mathrm{group}\times 100\% $$Reversion rates of each continuous parameter after 12 weeks (including reversion from prediabetes to normal glucose tolerance), calculated using the following formula: $$ \mathrm{Reversion}\ \mathrm{rate}=\mathrm{Cases}\ \mathrm{of}\ \mathrm{parameter}\ \mathrm{that}\ \mathrm{have}\ \mathrm{returned}\ \mathrm{to}\ \mathrm{normal}\ \mathrm{range}/\mathrm{Cases}\ \mathrm{of}\ \mathrm{each}\ \mathrm{group}\times 100\% $$

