### Participants

#### Screening of participants

Key entry criteria are adults who satisfy one or more American Diabetes Association (ADA) criteria for prediabetes, and do not include those diagnosed with diabetes. Among other criteria provided in Table 1, daily tobacco smokers were excluded due to unknown safety interactions with nutritional components in the study treatment. Previous research demonstrated an increased risk of lung cancer in smokers consuming β-carotene dietary supplements [95], and β-carotene is naturally present and sometimes highly abundant in many plants, including kudzu [96].

**Table 1 Tab1:** Inclusion and exclusion criteria

Critera	
Inclusion	Exclusion
Aged ≥18 years Fulfill prediabetes’ diagnostic criteria, determined by blood measurement values obtained within past 12 weeks Agree to continue with current diet and refrain from taking any new nutritional or herbal supplements during the study Agree to continue with current physical activity level throughout study period Able to understand and write English Voluntarily consent to the study and understand its nature and purpose including potential risks and side effects	Current daily use of any oral hypoglycemic medication or insulin injection Any current or previous diagnosis of diabetes (type 1 or type 2) Current daily use of any supplement containing the herbs in the study supplement Known allergies to any substance in the study supplement Current daily tobacco smoker Currently pregnant or breastfeeding, or planning to become pregnant in the next 12 weeks Myocardial infarction, vascular surgery, or stroke in the past year Refusal to provide consent for the study

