##### Diagnostic criteria

Prediabetes is classified as demonstrating any of the following, according to ADA guidelines [3, 97]:Hemoglobin A1c (HbA_1c_) of 5.7–6.4%Fasting blood glucose of 100–125 mg/dL2-h 75-g Oral Glucose Tolerance Test blood glucose value of 140–199 mg/dL 

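### The reversion rates are diluted by participants who cannot revert, the normal glucose limit overlaps the prediabetes range, and the diabetes incidence formula can count cases already present at baseline

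*Protocol article*

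**What the plan says.** **Entry.** Screening of participants admits "adults who satisfy one or more American Diabetes Association (ADA) criteria for prediabetes". Table 1 says that this status is "determined by blood measurement values obtained within past 12 weeks". Diagnostic criteria lists three alternatives: HbA1c of 5.7 to 6.4%, "Fasting blood glucose of 100–125 mg/dL", and a 2-hour "Oral Glucose Tolerance Test blood glucose value of 140–199 mg/dL". Source of participants names postprandial glucose as the third alternative and also allows inclusion by physician referral. Table 1 excludes people with a current or previous diagnosis of diabetes.

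**Reversion.** Additional indicators defines "Reversion rates of each continuous parameter after 12 weeks (including reversion from prediabetes to normal glucose tolerance". The numerator is those who have returned to the normal range. The denominator is all cases in the group.

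**Normal ranges.** Table 2 gives fasting glucose below 100.9 mg/dL and HbA1c below 5.7%. Neither Table 2 nor the text of Outcome measures lists a glucose tolerance test or a postprandial glucose value.

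**Diabetes incidence.** The formula is diabetes cases at the end of the study over all cases in the group. Table 2 lists progression to type 2 diabetes as a secondary outcome, judged by the 2016 ADA criteria.

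**The concern.** A reversion rate is read as the chance that an abnormal value becomes normal. That reading holds only if everyone in the denominator started abnormal, and here the entry rule does not ensure it for any single parameter. Table 2 has 13 continuous parameters (eight glycemic, four lipid, hs-CRP). Only fasting glucose and HbA1c are entry criteria at all, and either may be normal in a person who qualified on another test.

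Three further definitions blur the same rates. One glucose reading falls in two classes. The return to normal glucose tolerance has no listed test behind it. The incidence formula counts cases present at the end rather than cases that are new.

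The Discussion hopes that the product may restore glycemic parameters to normal ranges and help deter diabetes. These rates speak to those hopes most directly, so their definitions should measure what their names say.

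**Working it through.** The article states no reversion or incidence figure, so there is none to reproduce. The check sets the definitions against each other and works out what the formulas return.

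**1. Denominator.** Let *f* be the share of an arm abnormal on a parameter at baseline, and *r* the share of those who return to normal. The article gives neither, so both are assumptions. Counting only true returns, the whole-group rate is *f* × *r*, and the rate among those at risk is *r*.

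- *f* = 0.6, *r* = 0.5: 0.6 × 0.5 = 0.30, against 0.50 among those at risk.
- *r* = 0.40, with *f* = 0.3, 0.5, 0.7, 0.9: 12%, 20%, 28%, 36%, against 40% throughout.

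The dilution differs from parameter to parameter because *f* does, so the rates cannot be compared across the rows of Table 2.

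**2. Chance imbalance.** With 20 per arm (Sample size) and *f* = 0.6, the SD of the between-arm difference in the share abnormal is √(2 × 0.6 × 0.4 / 20) = 0.155. Multiplied by *r* = 0.5, this is 0.077, or about 8 points in the reversion difference. For illustration, 14 of 20 against 8 of 20 abnormal, with 50% reversion in both arms, gives 7/20 = 35% against 4/20 = 20%. That is a large imbalance: 30 / 15.5 = 1.94 SD.

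The 8 points are part of the ordinary sampling error of the whole-group rate. The total variance of the difference is 2 × 0.3 × 0.7 / 20 = 0.021, and the part due to imbalance is 0.077² ≈ 0.006.

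**3. Glucose limit.** The prediabetes range starts at 100 mg/dL and the normal range ends just below 100.9 mg/dL. Values from 100 to below 100.9 belong to both. In whole numbers this is one value (100) of the 26 from 100 to 125, or 1/26 = 3.8%. If fasting glucose is normally distributed with SD 8 mg/dL and mean 100, 105 or 110 (assumed), about 9%, 5% or 3% of people in the 100–125 range fall in the overlap. HbA1c has no overlap: normal is below 5.7% and prediabetes starts at 5.7%.

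Blood is drawn only at baseline and week 12, and missing values are filled by last observation carried forward. A dropout with a baseline reading of 100 mg/dL therefore ends in the normal class with no change.

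**4. Normal glucose tolerance.** A participant who qualified on the tolerance test alone has fasting glucose and HbA1c outside the prediabetes ranges at qualification. If that test is not repeated at week 12, this person's return from prediabetes either cannot be assessed or would be inferred from two markers that were never abnormal.

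**5. Diabetes incidence.** Only diagnosed diabetes is excluded, qualifying values may be up to 12 weeks old, and the text does not make the baseline sample an eligibility check. A participant with an undiagnosed diabetic-range value at the baseline draw, which persists or is carried forward, is a case at the end of the study and enters the numerator. One such person in 20 moves an arm's rate by 1/20 = 5 points. The article gives no basis for saying how often this would happen.

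**The case against.** Much of the case on the other side stands.

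- A reader might infer that whole-group division makes unchanged participants count as reverted. The formula does not say that. Its numerator is those who have *returned* to normal, and someone normal at baseline has not returned. On that wording the denominator only lowers the rate. False reverters would appear if the numerator were applied as normal at week 12: with *f* = 0.5 and no change in anyone, the rate would be 50%. The article does not define it that way.
- A reader might also infer that the incidence formula has the wrong denominator, or that the glucose limit or the missing tolerance test creates false diabetes cases. None of this follows. Diagnosed diabetes is excluded, so the whole group is the nominal at-risk set. Progression uses the ADA diabetes criteria, not the 100.9 mg/dL limit, and an absent test cannot add a case. Only the count of cases at study end is at fault, and Table 2's word *progression* suggests that new cases were meant.
- The rates are not biased between arms. Randomization balances baseline status in expectation; interpretation and some precision suffer.
- Data collection points says that all of them are shown in Fig. 1, which was not available. A week-12 tolerance test may be scheduled there, so it cannot be said that normal glucose tolerance will go unmeasured.
- The glucose overlap is one whole-number value, and reversion rates are additional indicators in a trial that calls itself proof-of-concept and exploratory.

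These points limit the size of the problem. They do not make the definitions right.

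**Conclusion.** The point holds as a fault in four definitions.

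- **Reversion denominator:** the reported rate is *f* × *r*, not *r*. It reads 30% instead of 50% at *f* = 0.6 and *r* = 0.5, and 12% to 36% instead of 40% over *f* = 0.3 to 0.9. All values of *f* and *r* are assumptions. Only the direction follows from the article.
- **Fasting glucose limit:** the article contradicts itself for readings from 100 to below 100.9 mg/dL. The effect is small.
- **Normal glucose tolerance:** no such test is among the listed outcomes. This remains a query until Fig. 1 is checked.
- **Diabetes incidence:** the formula as written counts cases already present at baseline. Each one is worth 5 points in an arm of 20.

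The harm is to what the rates mean and, modestly, to their precision. The primary comparisons of continuous glycemic markers do not use these rates.

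**What to change.** 1. For each parameter, compute reversion among participants outside the normal range on the baseline-visit sample.
2. Reconcile the fasting glucose limit in Table 2 with the 100–125 mg/dL range in Diagnostic criteria so that no reading falls in both classes.
3. Define reversion from prediabetes on the markers measured at both visits, fasting glucose and HbA1c, among participants abnormal on at least one of them at the baseline visit. If a week-12 tolerance test is scheduled, list it as an outcome; otherwise drop the reference to normal glucose tolerance.
4. Count only new cases of type 2 diabetes, and leave participants in the diabetic range at the baseline draw out of the incidence rate.

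The cost is a change of wording in Additional indicators, Table 2 and the analysis plan. The blood samples for fasting glucose and HbA1c are already drawn at both visits. The downside is smaller denominators: at *f* = 0.6, an expected 12 rather than 20 per arm. Because the effect is no longer diluted, this need not cost precision on the scale of true reversion. At *r* = 0.5 the SD of the between-arm difference is √(2 × 0.5 × 0.5 / 12) = 20.4 points with 12 per arm, against √0.021 / 0.6 = 24.2 points for the whole-group rate rescaled by *f*.
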